### 2.10. Statistical Analysis

Statistical analysis will be performed in three phases: verification of the success of randomisation in creating comparable groups of patients with HFpEF; exploration of outliers and extreme values; and assessment of the normality of the primary variables.

Analysis of covariance (ANCOVA) models will be used, with each outcome variable as the dependent variable and intervention as the fixed effect (1 = RIPC; 0 = CG), adjusted for baseline values, medication, age, sex, and socioeconomic status. The results will be presented as absolute changes from baseline to follow-up, along with 95% confidence intervals (CIs). Pairwise comparisons will be adjusted via the Bonferroni post hoc correction.

As a sensitivity analysis, a propensity score matching (PSM) approach will be applied to account for imbalances in baseline covariates between groups. This causal inference model estimates what would have occurred if all the subjects in both groups had shared the same baseline characteristics. Each participant will be matched with other comparable characteristics via a 0.40 calliper through the psmatch2 command.

All analyses will follow the intention-to-treat principle, with participants analysed in the groups to which they were originally assigned, regardless of adherence, in line with the CONSORT guidelines.

A cost-effectiveness analysis of RIPC from a societal perspective will also be conducted. Costs over the 3-month period will be compared with the costs of usual care for patients with HFpEF. Effectiveness will be calculated as the difference in arterial stiffness between the RIPC and control groups.

Statistical significance will be set at *p* < 0.05. All analyses will be conducted via STATA version 16.

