## Abstract

**Background/Objectives**: Heart failure with preserved ejection fraction (HFpEF) has increased in prevalence as the population ages and associated comorbidities increase. Remote ischemic preconditioning (RIPC) has been shown to provide protection against ischemic injury to the heart and other organs. Therefore, the aim of this project will be to analyse the effectiveness of RIPC in terms of arterial stiffness, endothelial function, diastolic function, and exercise capacity in patients with HFpEF. **Methods**: The PIRIC-FEp study will be a parallel, randomised controlled trial with two groups conducted at the Faculty of Nursing in Cuenca, University of Castilla-La Mancha. Individuals who are diagnosed with HFpEF and are older than 40 years, with a left ventricular ejection fraction ≥50% and a sedentary lifestyle, will be included. The exclusion criteria will include, among others, patients with noncardiac causes of heart failure symptoms, significant pulmonary disease, diabetes, peripheral vascular disease, or myocardial infarction within the previous three months. A sample size of 48 patients was estimated, with 24 for each group. Participants will be randomly allocated (1:1) to either the RIPC intervention group or the control group to evaluate the effects on arterial stiffness, endothelial function, diastolic function, and exercise capacity. Assessments will be conducted at baseline and after a three-month follow-up period. **Results**: The findings will be published in a peer-reviewed journal article. **Conclusions**: This study is important for daily clinical practice because it provides a new approach for the treatment of HFpEF patients via RIPC.

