## 2. Materials and Methods

### 2.1. Design

The PIRIC-FEp study will be a 2-arm, parallel-group RCT evaluating an RIPC intervention in patients with HFpEF over a 3-month period. The design of this study allows for the evaluation of the effectiveness of the therapeutic intervention and minimises selection bias. By including two parallel groups, one intervention group and one control group, treatment crossover is avoided, and the internal validity of this study is reinforced, facilitating a direct and reliable comparison between the two groups. This RCT protocol has been registered on ClinicalTrials.gov (NCT07024810).

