### 2.4. Randomisation

Participants will be randomly assigned (1:1) via EPIDAT version 4.2 software (Figure 1) to one of two groups: Group 1, RIPC; Group 2, the control group (CG). Prior to randomisation, screening will be performed, and all participants will be required to sign the informed consent form.

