#### 2.7.1. Primary Outcomes

Exercise capacity:-Six-Minute Walking Test (6MWT): This test will be conducted in a 30 m long corridor. The participants will walk back and forth along this section, which will be marked with cone-shaped markers placed 29 m apart, leaving 0.5 m at each end to facilitate turns. The test will be supervised by the examiner.

Endothelial function:-Carotid Intima-Media Thickness (CIMT): CIMT will be assessed via ultrasound using the Sonosite SII device, Bothell, WA, USA. CIMT is an independent predictor of future clinical events such as myocardial infarction and sudden cardiac death [40] and allows for the assessment of structural changes over time, facilitating the monitoring of atherosclerosis [41].

Arterial stiffness:-Pulse wave velocity (PWV), the radial augmentation index (rAIx), and the central augmentation index (cAIx): These measurements will be obtained via the SphygmoCor System (AtCor Medical Pty Ltd., West Ryde, NSW, Australia) while the patient is lying in a supine position. Pulse waves will be recorded from the carotid and femoral arteries. The rAIx is calculated as follows: (Second systolic peak [SBP2] − Diastolic blood pressure [DBP]) divided by (First systolic peak − DBP), multiplied by 100 (%). The cAIx is calculated as follows: central pulse pressure augmentation times 100 divided by pulse pressure. All indices will be derived directly from the respective devices.

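### The stated Bonferroni correction acts on pairwise comparisons, of which a two-arm trial with one follow-up has one per outcome, so error across the five primary outcomes is uncontrolled

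*Protocol article*

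**What the plan says.** Under "2.7.1. Primary Outcomes" the protocol article lists three domains and five measured variables. Exercise capacity is measured by the 6MWT and endothelial function by CIMT. Arterial stiffness has three measures: "Pulse wave velocity (PWV), the radial augmentation index (rAIx), and the central augmentation index (cAIx"). None is marked as the principal one.

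Section 2.10 gives the model: "Analysis of covariance (ANCOVA) models will be used, with each outcome variable as the dependent variable". The intervention enters as a two-level fixed effect (RIPC or control), with adjustment for baseline and other covariates. The same section sets significance at p < 0.05 and states one multiplicity rule: "Pairwise comparisons will be adjusted via the Bonferroni post hoc correction".

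On design, section 2.1 says "The PIRIC-FEp study will be a 2-arm, parallel-group RCT", and the Abstract says "Assessments will be conducted at baseline and after a three-month follow-up period". Section 2.9 sizes the trial at 0.05 and 90% power for flow-mediated dilatation, which is not one of the five primary outcomes.

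**The concern.** A Bonferroni correction of pairwise comparisons has work to do when a model yields several group contrasts, as with three or more arms. This trial has two arms and one post-baseline assessment, so there is one contrast per outcome and nothing to correct. The multiplicity that does exist lies across the five primary outcomes, and the stated rule does not reach it.

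Two things are at stake. A nominally significant result on any one of five primary outcomes could be reported as a positive primary finding with a false-positive risk well above 5%. And the Bonferroni sentence would lead a reader to believe that multiplicity had been dealt with. This matters more because the trial is small (48 participants) and section 2.7 says that the outcome assessors are not blinded.

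**Working it through.** **Inputs from the protocol article**
- Arms: 2 (section 2.1), allocated 1:1 (section 2.4).
- Assessments: baseline and one at three months (Abstract).
- Primary outcomes: 5 variables in 3 domains (section 2.7.1).
- Threshold: p < 0.05 (section 2.10). Sidedness is not stated; two-sided is assumed, in line with the 95% confidence intervals.
- Sample size: 20 per group before dropout, 90% power, 0.05, for flow-mediated dilatation (section 2.9).

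**Step 1. What the stated rule does**
- Pairwise contrasts among k groups: k(k − 1)/2. With k = 2 this is 2 × 1/2 = 1.
- Baseline is a covariate in the ANCOVA and there is one follow-up, so time adds no further group contrast.
- Bonferroni threshold per outcome: 0.05/1 = 0.05, which is unchanged.

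**Step 2. Error across the primaries if RIPC has no effect**
- Five independent tests: 1 − 0.95^5 = 1 − 0.774 = 0.226, or 22.6%.
- Three independent tests, one per domain: 1 − 0.95^3 = 1 − 0.857 = 0.143, or 14.3%.
- Correlated outcomes: the article gives no correlations, so these are assumptions. The figures are simulated two-sided tests at 0.05 on five correlated normal statistics.

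| Assumed correlation structure | Chance of at least one false positive |
|---|---|
| rAIx–cAIx 0.8, other pairs 0.1 | 20.7% |
| rAIx–cAIx 0.9, other pairs 0.3 | 19.0% |
| rAIx–cAIx 0.95, other pairs 0.5 | 16.6% |
| Three stiffness measures 0.7, the rest independent | 19.7% |
| All five pairs 0.5 | 18.3% |
| All five pairs 0.9 (extreme) | 10.2% |

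Even the extreme case is about twice the nominal 5%.

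**Step 3. Error after a correction across outcomes**
- Bonferroni over five: 0.05/5 = 0.01 each. If independent, 1 − 0.99^5 = 0.049, or 4.9%. It is at most 5% under any correlation.
- Holm uses 0.01 for the smallest p-value and less strict thresholds after that. It gives the same familywise guarantee and never has less power than Bonferroni.

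**Step 4. Power cost, as an illustration only**
- Section 2.9 gives no difference or SD, so its 20 per group cannot be reproduced. Solving backwards for 20 per group, two-sided 0.05 and 90% power with a t test gives a standardised difference of 1.05. That value belongs to flow-mediated dilatation and is an assumption for any of the five primaries.
- Unadjusted t test, 1.05 SD, 20 per group: power is 90% at 0.05 and about 73% at 0.01.
- Baseline adjustment divides the residual SD by a factor that depends on the baseline-to-follow-up correlation r: the effective difference becomes 1.05/√(1 − r²). At 0.01, power is about 86% for r = 0.5 and about 97% for r = 0.7 (both r assumed).

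**The case against.** The strongest case on the other side has four parts.

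- **It belongs in the analysis plan.** An article condenses a fuller protocol, and a testing order or success rule is often left to the SAP. This stands to the extent that the absence of a hierarchy is not itself the finding. The finding is that the article does state a multiplicity rule, and that rule cannot act on the design described.
- **The sentence may mean something else.** The authors may have meant correction across outcomes, or within-group change contrasts, and corrected p-values are also compared with 0.05. The general threshold alone therefore does not prove that the outcomes go uncorrected. But the text says pairwise comparisons, directly after a two-group model, and on either alternative reading it would still need rewording. If correction across five outcomes was intended, the sample size at an undivided 0.05 does not reflect it.
- **The outcomes are correlated, or the family is three domains.** Both reduce the inflation. Neither brings it near 5%.
- **The power cost is not known for these outcomes.** This is right. A reader might take the fall from 90% to 73% as the cost in this trial. The document does not support that, because the effect is back-solved for a variable outside the five and the calculation ignores the planned baseline adjustment.

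Two further inferences go beyond the text. A reader might conclude that one significant primary is the declared criterion for efficacy; the article states no such criterion and only leaves the possibility open. A reader might also conclude that PWV has to be the single primary. The reasons usually offered do not single it out: section 2.7.1 says all the indices come directly from devices, and the cost-effectiveness measure in section 2.10 is arterial stiffness, a heading that covers PWV and both augmentation indices.

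**Conclusion.** The concern holds. As written, the Bonferroni rule leaves each of the five primary outcomes tested at 0.05 and gives no protection across them. That the factor is 1 follows from the design alone and needs no assumption.

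The size of the inflation does depend on assumptions. The independence figure of 22.6% should not be quoted as the trial's actual error rate: the two augmentation indices can be expected to correlate, and 17-21% is the more plausible range under the correlations assumed here. Every scenario examined is at least about twice 5%. All figures assume two-sided tests and no effect of RIPC on any of the five outcomes.

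**What to change.** In section 2.10, replace the pairwise sentence with a rule that acts across the primary outcomes, for example: the five primary outcomes will be tested with the Holm procedure at a familywise two-sided level of 0.05.

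Alternatively, before any outcome data are analysed, the sponsor names one primary outcome at two-sided 0.05, or one per domain under Holm (with three, the first threshold is 0.05/3 = 0.0167), and makes the rest secondary. PWV is one option; the choice is the sponsor's. Either way, the protocol, registry entry and SAP should carry the same wording.

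The cost in text is small. The scientific cost is less power per outcome under Holm, or fewer outcomes able to carry a confirmatory claim. Because section 2.9 was calculated for flow-mediated dilatation, power should be recalculated for whichever outcome or outcomes remain primary, at the threshold they will face and with the planned baseline adjustment.

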### 2.11. Mitigation Strategies

Heterogeneity among participants.
○To reduce heterogeneity among participants, the established inclusion and exclusion criteria will be rigorously applied, thereby ensuring a more homogeneous sample.

Dropouts and missing data
○Qualified nursing staff from the research team will be responsible for training participants in the correct application of the therapy, as well as monitoring follow-up diaries and providing reminders via weekly phone calls and biweekly visits to ensure adequate compliance and minimise losses during follow-up. In addition, analyses will be conducted according to the intention-to-treat principle, meaning that all participants will be included in the primary analysis, regardless of whether or not they complete the intervention. With respect to the treatment of missing data, appropriate statistical methods, such as imputation techniques, can be applied to reduce the bias associated with missing information.

Small sample size.
○Although the sample size is small, it has been calculated on the basis of previous estimates and a dropout rate of 20%, which has been incorporated into the calculation to ensure the minimal statistical power required to detect relevant effects.

Exercise tolerance may be influenced by participants’ daily activities.
○Participants will be instructed to maintain their usual lifestyle during their involvement in this study. To monitor this, measurements will be taken via activity trackers, the 6MWT, and self-reported physical activity questionnaires.

Lack of blinding.
○The absence of blinding in both participants and research staff could influence the subjectivity of some assessments. To mitigate this limitation, objective measures, such as anthropometric parameters, blood pressure, biochemical markers, muscle strength tests, and exercise capacity assessments, among others, will be included. Similarly, to reduce bias resulting from the lack of blinding in the research team, standardised protocols for data collection will be applied.

Potential bias.
○To mitigate potential bias, confounding variables such as medication, age, sex, and socioeconomic status will be considered in the analyses.

## 3. Results

The results will be published as a peer-reviewed article.

## 4. Discussion

The main aim of this study was to evaluate the effectiveness of RIPC in patients with HFpEF by assessing its impact on arterial stiffness, endothelial function, diastolic function, and exercise capacity. The secondary objectives are as follows: (1) To compare the effectiveness of RIPC on QoL in patients with HFpEF and (2) to analyse the cost-effectiveness of RIPC versus conventional treatment in patients with HFpEF.

### 4.1. RIPC, HFpEF, and Exercise Capacity

HFpEF is characterised by cardiovascular abnormalities such as myocardial stiffness and fibrosis, which may contribute to reduced exercise tolerance and symptoms such as oedema or chronotropic incompetence [43]. RIPC has been shown to be effective in improving exercise capacity in healthy individuals through both local (i.e., limb) and remote effects (via the cardiovascular or nervous system) [8]; however, it has not been explored in individuals with pathologies, such as HFpEF.

### 4.2. RIPC, HFpEF, and Cardiac Function

HFpEF is associated with abnormal cardiac function, including increased left ventricular stiffness, leading to impaired relaxation during diastole and resulting in elevated pressure and/or impaired filling. The effect of RIPC on cardiac function has been investigated in patients with coronary artery disease [44], in whom it was found to have a neutral effect. However, the influence of RIPC on cardiac function has rarely been explored and has not been studied in patients with HFpEF. Given the remote cardiovascular and neurological effects of RIPC, beneficial results from this intervention could be expected.

### 4.3. RIPC, HFpEF, and Endothelial Function

Endothelial dysfunction is considered an early marker in HFpEF, as it occurs early in the disease and manifests as a loss of cardiac microvascular density, which may be influenced by comorbidities commonly associated with HFpEF [45]. Previous studies have shown that RIPC can improve endothelial function via local and remote ischaemia-reperfusion mechanisms [46], and these effects may improve exercise capacity by preserving the supply of oxygen and energy substrates to skeletal muscles.

### 4.4. RIPC, HFpEF, and Arterial Stiffness

Arterial stiffness, particularly of the aorta, increases the load on the left ventricle, adversely affecting its structure and function. These changes contribute to the development of diastolic dysfunction, which is a key factor in HFpEF. Moreover, increased carotid–femoral pulse wave velocity has been associated with a greater risk of heart failure [47]. Given the contribution of arterial stiffness to HFpEF, interventions that target this parameter may prove beneficial in its management. To date, RIPC has shown inconclusive results in patients with peripheral arterial disease [48] and angina pectoris [42]; however, its effects have not yet been demonstrated in individuals with HFpEF.

### 4.5. Physiological Mechanisms of RIPC

RIPC contributes to the optimisation of mitochondrial function by increasing ATP synthesis, improving mitochondrial respiratory efficiency, reducing the opening of the mitochondrial permeability transition pore (mPTP), and decreasing the production of reactive oxygen species (ROS) [49]. Furthermore, it has been associated with improved vascular endothelial function and an increased release of nitric oxide, facilitating a reduction in both cardiac preload and afterload [50]. Additionally, evidence suggests that RIPC-induced mitochondrial improvement in T lymphocytes may protect the myocardium by exerting anti-inflammatory effects and mitigating ischaemia-reperfusion injury-related damage [51].

### 4.6. Potential Limitations

Some potential limitations of this study must be considered: (1) this study will be conducted with individuals from a single province (Cuenca), which limits the generalisability of the findings to the broader population; (2) although the proposed sample size is not very large, it may not be fully achieved, which would reduce the statistical power of this study; (3) the intervention will be carried out by the participants themselves following prior instructions provided by a healthcare professional. This could lead to errors in implementation and difficulties in monitoring adherence, potentially affecting the effectiveness of the RIPC. (4) The intervention will last three months, so even if effects are observed at the end of this period, they could be temporary. Therefore, longer-term studies will be necessary to assess the long-term effect of the RIPC; and (5) the absence of blinding in participants can affect subjective assessments, such as self-report questionnaires, and favour the emergence of biases associated with the placebo effect. For its part, the lack of blinding of the research team, in addition to affecting subjective assessments, could influence the way in which data are collected, recorded, or interpreted, thereby jeopardising the objectivity of this study.

## 5. Conclusions

This study has clinical relevance, as HFpEF has a high prevalence, which is expected to continue to increase in the coming years. This research will provide healthcare professionals with a novel approach to the treatment of HFpEF via RIPC, with the aim of improving functional capacity, cardiac function, endothelial function, and arterial stiffness.

## Figures and Tables

**Figure 1 biomedicines-13-01923-f001:**
[figure not shown]
Remote ischaemic preconditioning (RIPC) and control group (CG) protocols.

**Figure 2 biomedicines-13-01923-f002:**
[figure not shown]
Flowchart for patient inclusion and follow-up: screening, inclusion and exclusion, randomisation, baseline testing, and postintervention testing.

**Table 1 biomedicines-13-01923-t001:** Inclusion and exclusion criteria.

Inclusion Criteria	Exclusion Criteria
**1. Diagnosis of HFpEF (according to 2021 ESC criteria):** **Signs and symptoms of HF** **Left ventricular ejection fraction (LVEF) ≥ 50%** **Objective evidence of structural and/or functional cardiac abnormalities consistent with left ventricular diastolic dysfunction and/or elevated left ventricular filling pressures, including elevated natriuretic peptides** **2. Sedentary people (men and woman) (structured exercise <2 × 30 min/week)** **3. Age ≥ 40 years** **4. Written informed consent** **5. Clinically stable for at least 6 weeks** **6. On optimal medical therapy for ≥6 weeks**	1. Noncardiac causes of HF symptoms: - Significant valvular or coronary artery disease - Uncontrolled hypertension or arrhythmias - Primary cardiomyopathies 2. Significant pulmonary disease (FEV1 < 50% predicted, GOLD stage III–IV) 3. Inability to exercise or conditions that may interfere with the exercise intervention 4. History of myocardial infarction in the past three months 5. Patients with diabetes and/or peripheral vascular disease * 6. Signs of ischaemia during maximal cardiopulmonary exercise testing 7. Comorbidities that may affect 1-year prognosis 8. Enrolment in a different clinical study

ESC: European Society of Cardiology. HF: Heart failure. HFpEF: Heart failure with preserved ejection fraction. FEV1: Forced expiratory volume in 1 s. GOLD: Global Initiative for Chronic Obstructive Lung Disease. * Exclusion criterion 5 specifies that patients with diabetes and/or peripheral vascular disease were excluded. In the case of type 2 diabetes, this decision was based on evidence indicating that RIPC does not consistently confer cardioprotective effects in this population. This limitation is attributed to mitochondrial dysfunction caused by elevated levels of glycosylated proteins in diabetic patients, which interferes with the protective mechanisms typically activated by RIPC [35]. With regard to peripheral vascular disease, patients were excluded because the application of RIPC is contraindicated due to the risk of local ischaemia or tissue damage in the affected limbs [36].

